### Qualitative process evaluation

Qualitative research can contribute depth of understanding on why programmes achieve the effects that they do [20,21] and we will use semi-structured interviews with pharmacists and trial participants to determine key factors in relation to initial engagement, ongoing participation and overall response to the programme and the trial. We will purposively selected 4 to 6 pharmacists, some of whom recruited none or few participants and some who recruited many. Semi-structured interviews will investigate factors that influence pharmacist recruitment to the programme and clinical trial, response to training issues, their experiences of implementing the reduction programme and recruiting. The interviews will cover the factors that hindered or facilitated pharmacists' ability to recruit participants and their perceptions of smokers' reactions to behavioural support and medication provided within the programmes. Delivery of the overall programme and behavioural support will be explored including how support delivery is organised within the pharmacy and by whom. Pharmacists will be asked about their understanding of tobacco addiction and its treatment and about tobacco control in general and where smoking reduction fits in, because there is evidence from studies among GPs that these broader attitudes affect the clinical treatments doctors give their patients.

Trial participants will be approached by the research fellow who will select some who have used each of the permutations of support/no support and short/standard reduction programmes. Participants who drop out, reduced and quit smoking, reduced only, or achieved no success with the programmes will be approached for interview. We expect to enrol about 2 people per permutation i.e. about 26 in total. The interviewer will enquire about their motivation for using the programme, their experience of it, and what if any changes occurred to their smoking and why they thought they occurred. Responses to trial follow-up methods will also be explored.

The interviews will be audio-recorded and transcribed with respondents' permission. Interviews will be conducted by the research fellow at a time and location convenient to respondents and trial participants will be offered financial compensation of £20 for their time to acknowledge their contribution to the study. The interviews will be systematically read and interpreted, comparing key features of emergent findings and concepts to minimise bias in interpreting data [22,23]. We will use open coding to identify emergent themes, and categories within these. We will interweave data collection and analysis, conducting later interviews after initial data analysis to provide insights for refining each theme and category.

### Trial Medication

Participants are encouraged to use both a nicotine patch and a short-acting (acute) form of NRT and those who are eligible to pay a prescription charge on the NHS (£7.20) will have to do so for each item dispensed. Combination patch plus acute NRT is becoming a standard dosing regimen for cessation treatment [24], with manufacturers now packaging combined products. This is because of superior efficacy in enhancing cessation of combination over single form NRT [24]. There are fewer trials of NRT in smoking reduction, too few to assess the relative efficacy of the different NRT preparations [2], and no trials of combination NRT versus single form NRT. Therefore the dose regimen is based upon limited trial evidence and extension of the evidence from its use in cessation (reduction to zero cigarettes). A systematic review of placebo controlled short-term trials of nicotine patch and acute NRT show that both reduce daily cigarette consumption in people who are not trying to reduce their smoking and people who are [25]. Both patch and acute NRT appear equally effective in assessing reduction. One long-term trial allowed people free choice between patch, gum, and inhaler and found that gum produced the greater reduction of cigarettes than patch or inhaler [26]. The rationale for patch use is that smokers find regular use of the patch very easy, with typically very high levels of adherence [27], while acute NRT dosing is often sub-optimal [28]. However, acute NRT provides a direct behavioural replacement of cigarettes (such as 'have a piece of gum when you would ordinarily smoke') and this appears important in smoking reduction [29]. This population have relatively low interest in cessation and might need to continue pharmacotherapy for up to a year, so a combination approach seems most likely to produce optimal adherence to regimen and optimal efficacy.

There is no foolproof way to give a person exactly the right dose of nicotine. However, serious problems from too much nicotine replacement are uncommon in smokers. All smokers have had episodes of rapid smoking and can easily identify symptoms resulting from too much nicotine and can cut back. Furthermore, nicotine replacement, particularly in the form of patches, delivers nicotine in a very slow form. Experience of using high dose nicotine patches (up to 63 mg daily) shows that side-effects from 'overdose' are unusual when nicotine is given slowly to smokers [25]. On the other hand, there is good evidence that the smoking reduction without NRT or with an inadequate dose of NRT is much less effective [2]. Bearing these considerations in mind, we propose the following dosing algorithm.

### Initial patch dose

• < 10 cigs/day - 7 mg/24 hour patch or 5 mg/16 hour patch

• 10-19 cigs/day - 14 mg/24 hour patch or 10 mg/16 hour patch

• 20+ cigs/day - 21 mg/24 hour patch or 15 mg/16 hour patch

This dosing guideline should be modified according to exhaled carbon monoxide (CO) reading and patient preference.

• < 10 ppm - 7 mg/24 hour patch or 5 mg/16 hour patch

• 10-19 ppm - 14 mg/24 hour patch or 10 mg/16 hour patch

• ≥20 ppm - 21 mg/24 hour patch or 15 mg/16 hour patch

The patch dose from cigarettes per day will be estimated by exhaled CO. If there is a conflict, the pharmacist should generally use the higher suggested dose. Pharmacists are emphasised that CO levels are typically lower in the morning rising steadily through the day; therefore the dosing guidelines are only approximate

Participants will be advised to remove the patch at night and replace with a new patch each morning i.e. use under 16 hours only, even if the product is a 24 hour patch. One of the most frequent side-effects of patch is vivid dreams or insomnia and using over 16 hours prevents this, with no decrement in efficacy [24]. Reducing adverse reactions is a key aim of treatment that might last for nine months.

### Initial short-acting NRT dose

Participants can have free choice of nicotine inhalator, 2 mg gum, 2 mg sublingual tablets, 2 mg lozenges, or nasal spray.

• For gum, lozenge, or sublingual tablets, participants should replace each missed cigarette with one of their chosen product.

• For nasal spray, participants should take one spray in each nostril to replace each missed cigarette.

• For inhalator, patients should puff as often as is needed. As a rough guide, 40-80 puffs on the inhalator replace one cigarette.

Participants will be strongly encouraged to use both a patch and a short-acting form of NRT concurrently. However, participation in the study depends upon willingness to use NRT in general, so individuals prepared to use only one form of NRT will be allowed to participate. Participants will choose the preferred product together with pharmacists. Participants are allowed to change their NRT at anytime during the trial.

### Dose alteration procedure

Overdose of nicotine is unlikely in clinical practice using the above products. There is still a common perception that it is inadvisable to use NRT and smoke, although the data suggest that this is not true [2,27]. This belief is reinforced by the old labelling that advised people not to smoke while using NRT. The Medicines and Healthcare Regulatory Authority (MRHA) has removed this from all products, but the perception is slower to change, so we will advise pharmacists to reassure patients.

Although nausea or indigestion can be symptoms of overdose, they are common adverse events to oral or nasal NRT and are an unreliable guide to overdose. Likewise, some symptoms such as agitation or restlessness are both symptoms of nicotine withdrawal suggesting under-dosing and of overdose. Pharmacists will therefore be advised to look for definite symptoms of:

• Muscular twitching

• Dizziness

• Confusion

• Rapid pounding heart

• High blood pressure

• Vomiting

• Weakness

Assuming overdose symptoms are not present, then the option for dose alteration will be either to continue with the present patch dose, or to increase the patch dose to the next step i.e. from 7 mg to 14 mg or 14 mg to 21 mg or from 5 mg to 10 mg or 10 mg to 15 mg or 15 mg to 25 mg. Criteria for suggesting an increased dose of patch are as follows

• The patient wants to reduce smoking further

• The patient is finding smoking reduction difficult because s/he is feeling irritable, edgy, and urges to smoke in periods when smoking is 'not allowed' by the programme they are following.

The short-acting forms of NRT have no upper limit of dose for all practical purposes because practical considerations (such as the need to eat), or local irritation from the products, and the sensation of having used too much nicotine within a short time of using the product, naturally limit the dose consumed. The patient will be advised to replace each additional missed cigarette with a short-acting form of NRT as described in the initial dosing. Should a person find that going without cigarettes is difficult; the dose of short-acting NRT should be increased in the following way:

• For gum or lozenge, increase the dose from 2 mg lozenge to 4 mg lozenge.

• For sublingual tablets, participants should use two microtabs at a time.

• For nasal spray, participants should administer two sprays in each nostril to replace each missed cigarette.

• For inhalator, patients should puff as often as is needed.

• Modification of medication regime

Participants who have problems with insomnia or difficulties with vivid dreams will use the patch for 16 hours daily, not 24 hours. Participants who have skin reactions to the patch that are not controlled by switching preparations, emollient and hydrocortisone cream will switch to short-acting NRT only.

• Participants who become pregnant may have their dose adjusted in line with NICE guidance(8) and in accord with the wishes of the participant.

• Participants who show symptoms of overdose will have the dose reduced.

• Participants who give up on their reduction attempt will cease using NRT.

• Participants who experience adverse reactions or adverse events will stop using NRT products, definitively or temporarily, when deemed necessary by the study physician

• Participants who stop the treatment early will not be replaced, and they will be followed-up like the other participants.

Pharmacists are advised to apply same guidelines for patients who come to them with any above issues if they are in the arm of the study which does not give behavioural support.

### Concomitant medication

All medications will be permitted for use concurrently, except those that are proven to help smoking cessation (bupropion, nortriptyline, mecamylamine, reserpine, varenicline), or medications that are unlicensed and for which no interaction data with NRT are available. The NRT itself is aimed at the relief of symptoms of nicotine withdrawal. Should adverse skin reactions occur with the use of the patch, advice will be given on the use of over the counter emollients and 1% hydrocortisone cream, as is standard. Data on all concomitant medication will be recorded.

## Discussion

The findings from the proposed trial are timely and highly relevant in public health as there is a recognized need to support smokers who feel unable to quit to reduce their smoking instead. The Department of Health (DH) proposed a new tobacco control strategy that envisaged 'tailored quit plans' meaning smoking reduction as an intermediate goal without necessarily committing to abstinence. Although the DH has committed to harm reduction, there is no trial showing that allowing reduction alongside cessation leads to greater health benefits than offering abrupt cessation only. This is a pilot study to assess the feasibility of offering smoking reduction programme within pharmacies that offer naturalistic setting to show population benefit from these programmes. In addition, findings from this trial will inform the development of evidence-based treatment for smokers who want to reduce and best approaches to engage reluctant quitters onto the programme.

### Procedures for handling the data

#### Data Management

The trial will run as part of the portfolio of trials in the Primary Care Clinical Research and Trials Unit (PCCRTU), an NIHR recognised trials unit in Primary Care Clinical Sciences at the University of Birmingham. The data management will be run in accord with the standard operating procedures (SOPs), which are fully compliant with the Data Protection Act and International Conference on Harmonisation (ICH) and Good Clinical Practice (GCP). The source documents for the trial will be the case report forms (CRFs) which will be stored in the pharmacies in a locked cabinet in a locked office. The trial database will be securely held and maintained by the PCCRTU. Data cleaning will take place by a series of logical checks on the electronic data. (For example, a person cannot be recorded as prolonged abstinent smoker at 6 months if they were not in such a state at 8 weeks). Discrepant records will be checked with the source documents and the database amended if necessary. On completion of the trial and data checking, the CRFs will be transferred to Modern Records, a secure archiving facility at the University of Birmingham, where they will be held for 15 years and then destroyed. The database will be anonymised and a secure compact disc containing the link between identification number and patient identifiable information will be stored in modern records.

### Data Protection and Confidentiality

Data will be kept in accordance with the Data Protection Act and the trial registered with the Data Protection Act website at the University of Birmingham. The SOPs of the trials unit will be followed, which are designed to protect patient confidentiality. Patient identifiable data will be shared only within the clinical team on a need-to-know basis to provide clinical care and ensure good and appropriate follow up. Patient identifiable data will also be shared with the GP and approved auditors from the Research Ethics committee (REC), NHS Research and Development, or the MHRA will also be able to see patient identifiable information. Otherwise, confidentiality will be maintained and no one outside the trial team will have access to either the CRFs or the database. No data relating to individuals will be identified in publications.

### Ethical approval

The trial will be conducted in compliance with the principles of the Declaration of Helsinki (1996), the principles of ICH-GCP and run in accord with EU Clinical Trials Directive and all of the applicable regulatory requirements. The study protocol and other documentation have been approved by the Birmingham East, North and Solihull Research Ethics Committee, 14^th ^of June 2010 (REC reference number: 10/H1206/22) and amendment on 21 November 2011 (Amendment number: AM01). Any subsequent protocol amendments will be submitted to the REC for approval and the other bodies if necessary. We will comply with ICH-GCP Guidelines over the reporting of adverse events, serious adverse events, and suspected serious adverse reactions (SUSARS). In addition we will provide the REC with progress reports as well as a copy of the Final Study Report.

### Dissemination of the results

The trial results will be written up for submission to peer reviewed scientific journals and presented in national and international conferences. No data relating to individuals will be identified.

## Appendix 1 Adverse Event Reporting

### Definitions

#### B.1. Adverse event

An AE is any untoward medical occurrence in a clinical investigation participant administered a product or medical device; the event need not necessarily have a causal relationship with the treatment or usage. Examples of AEs include but are not limited to:

• abnormal test findings,

• clinically significant symptoms and signs,

• changes in physical examination findings,

• hypersensitivity, and

• progression/worsening of underlying disease.

Additionally, they may include the signs or symptoms resulting from:

• drug overdose,

• drug withdrawal,

• drug abuse,

• drug misuse,

• drug interactions,

• drug dependency,

• exposure in utero.

Failure of expected pharmacological action or therapeutic benefit alone (i.e. lack of efficacy) is not necessarily an AE.

#### B.2. Definition of serious adverse event

A serious adverse event or serious adverse drug reaction is any untoward medical occurrence at any dose that: results in death, is life-threatening (immediate risk of death), requires inpatient hospitalisation or prolongation of existing hospitalisation, results in persistent or significant disability/incapacity, and/or results in congenital anomaly/birth defect. An important medical event may not be immediately life-threatening and/or result in death or hospitalisation. However, if it is determined that the event may jeopardize the participant and may require intervention to prevent one of the other outcomes listed in the definition above, the important medical event should be reported as serious. Examples of such events are intensive treatment in an accident and emergency department or at home for bronchospasm; blood dyscrasias or convulsions that do not result in hospitalisation; or development of drug dependency or drug abuse. Serious adverse events will be those that occur during the period of medication use or within 7 or more days of ceasing medication use.

#### B.3. Definition of suspected serious adverse reaction (SSAR)

Means an adverse reaction that is classed as serious and which is consistent with the information about the medicinal product in question set out (in the case of a licensed product, in the summary of product characteristics for that product.)

#### B.4. Definition of suspected unexpected serious adverse reaction (SUSAR)

Means an adverse reaction that is classed as serious and which is not consistent with the information about the medicinal product in question set out (in the case of a licensed product, in the summary of product characteristics for that product)

#### B.5. Monitoring and reporting adverse events

NRT is a well tried and tested medication and there are minor common and well known side-effects that it will not be practical or useful to record. For example, oral NRT almost universally causes burning in the mouth that most people find initially unpleasant but become used to in due time. Where adverse events are listed in SPC as expected and are classified as mild, pharmacists will not be required to record these on the adverse event form.

For all other adverse events (i.e. moderate or severe or possibly serious), the investigator will pursue and obtain information adequate both to determine the outcome of the adverse event and to assess whether it meets the criteria for classification as a serious adverse event requiring immediate notification to the sponsor, the NHS R&D office, and the research ethics committee. The investigator will assess causality. For adverse events follow-up by the investigator is required until the event or its sequela resolve or stabilise.

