#### B.6. Severity Assessment

The treating clinician or investigator will use the adjectives mild, moderate, or severe to describe the maximum intensity of the adverse event. For purposes of consistency, these intensity grades are defined as follows:

• Mild- Does not interfere with participant's usual function.

• Moderate- Interferes to some extent with participant's usual function.

• Severe- Interferes significantly with participant's usual function.

Note the distinction between the severity and the seriousness of an adverse event. A severe event is not necessarily a serious event. For example, a headache may be severe (interferes significantly with participant's usual function) but would not be classified as serious unless it met one of the criteria for serious adverse events, listed above.

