#### B.8. Causality Assessment

The pharmacist's or investigator's assessment of causality must be provided for all adverse events (serious and non-serious). An investigator's causality assessment is the determination of whether there exists a reasonable possibility that the investigational product caused or contributed to an adverse event. If the investigator's final determination of causality is unknown and the investigator does not know whether or not investigational product caused the event, then the event will be handled as "related to investigational product" for reporting purposes. If the investigator's causality assessment is "unknown but not related to investigational product", this should be clearly documented in the CRF. In addition, if the investigator determines a serious adverse event is associated with trial procedures, the investigator must record this causal relationship, as appropriate, and report such an assessment in accordance with the serious adverse event reporting requirements, if applicable.

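### The recording waiver for mild, expected adverse events makes no exception for events that change NRT treatment, and it conflicts with the rule that every adverse event gets a causality assessment

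*Protocol article*

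**What the plan says.** Four parts of the protocol article bear on this point.

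- **Recording (Appendix 1, B.5).** The rationale is that "there are minor common and well known side-effects that it will not be practical or useful to record". The rule itself reads: "Where adverse events are listed in SPC as expected and are classified as mild, pharmacists will not be required to record these". The text then continues: "For all other adverse events (i.e. moderate or severe or possibly serious), the investigator will pursue and obtain information adequate".
- **Severity (B.6).** The grade rests on function alone: "Mild- Does not interfere with participant's usual function". Any interference, even partial, makes the event moderate.
- **Treatment changes (Dose alteration procedure).** On overdose, the text says "Pharmacists will therefore be advised to look for definite symptoms of" and gives seven symptoms. Later it says: "Participants who show symptoms of overdose will have the dose reduced". The same list shortens patch wear for insomnia or vivid dreams, moves participants with uncontrolled skin reactions off the patch to short-acting NRT, and lets the study physician stop NRT for adverse reactions.
- **Definition and causality (B.1, B.8).** B.1 counts signs or symptoms of "drug overdose" among adverse events and excludes nothing for being mild or expected. B.8 says that the pharmacist's or investigator's "assessment of causality must be provided for all adverse events (serious and non-serious".

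**The concern.** The waiver is wider than its reason. Mouth burning that passes is not worth a form. An event that made the pharmacist reduce a dose or change a product is a different matter, yet B.5 treats both alike if the event is mild and listed.

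Under Trial Outcomes the protocol promises to examine adverse events and drop-outs as part of deciding what needs improving before a definitive trial. Under Trial Medication it says that the dosing regimen rests on limited trial evidence and on extrapolation from cessation. Reactions that changed treatment are the tolerability information that such a review needs most. The Sample size section has the amount of NRT used recorded by arm, but an amount does not show why use changed.

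The second problem is internal consistency: B.5 and B.8 cannot both be followed to the letter.

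**Working it through.** No arithmetic in the plan bears on this point, so the check sets the rules side by side.

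**Step 1: what B.5 waives.** An event escapes the form only if it is both (a) listed in the SPC as expected and (b) mild. Whether treatment changed is not a condition.

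**Step 2: what changes treatment.**

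| Reaction in the Dose alteration procedure | Effect on NRT | Severity threshold stated? |
|---|---|---|
| Overdose symptoms | Dose reduced | None |
| Insomnia or vivid dreams | Shorter patch wear | None beyond having problems with them |
| Skin reactions | Patch dropped, short-acting NRT only | Yes, in effect: not controlled by other measures |
| Other adverse reactions or events | Temporary or permanent stop | Study physician's judgement |

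None of the four uses the B.6 grades. A mild event can therefore meet a treatment-change rule. If it is also SPC-listed, B.5 requires no entry.

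**Step 3: does the gap depend on overdose symptoms?** No. Initial patch dose names vivid dreams or insomnia among the most frequent patch side-effects, and skin reactions can lead to a change of product. One qualification applies: the same section already advises night-time removal for everyone, so the shorter-wear route may seldom be used.

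**Step 4: B.5 against B.8.** B.8 requires a causality assessment for all adverse events, and B.1 does not remove mild or expected events from that set. An assessment cannot be documented for an event that was never entered. The two rules conflict for every event that B.5 waives, whatever the SPC contains.

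**Step 5: a loose end in B.5.** The gloss on the remaining events names moderate, severe and possibly serious ones. A mild event that is not SPC-listed is neither waived nor named among those to be pursued.

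**Step 6: size.** The expected number of participants whose treatment-changing reaction goes unrecorded is

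160 × P(treatment-changing reaction) × P(mild, given such a reaction) × P(SPC-listed, given mild) × P(pharmacist does not record, given no duty to).

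Only the planned 160 is in the document. The product is zero if no such reaction is both mild and listed, and the article gives nothing from which to set an upper figure short of 160. Putting guesses into the other four terms would say nothing about this trial.

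**The case against.** The strongest reply is that the waiver is deliberate and sensible. NRT is a licensed, well-known product, the trial is a feasibility pilot, and tolerability is not among its stated objectives. Both conditions must hold, so anything that interferes with usual function even partly is still pursued, and SAEs and SUSARs are reported separately. B.8 can be read as applying only to events that enter the reporting system. Participants who drop out are among those approached for interview, and early stoppers stay in follow-up. The full case report form, which is not shown, may log dose changes with reasons.

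Most of this stands. It supports keeping the waiver and treating the point as minor. It does not explain why an event that altered treatment should be exempt. Interviews with about 26 participants are no substitute for a record on all 160. The narrow reading of B.8 is probably what was meant, but the text says otherwise.

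A reader might infer more: that the waiver covers the seven overdose symptoms as a class, so the trial will under-report overdose. The document does not support this. It nowhere says that those symptoms are SPC-listed, and several, such as confusion or vomiting, would rarely be graded mild. The Dose alteration procedure also separates them from nausea and indigestion, which it treats as common NRT effects, and calls overdose unlikely. Nor is overdose the only drug risk pharmacists must act on, as the table shows.

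**Conclusion.** The point holds in a limited form. B.5 leaves a route by which a mild, SPC-listed event can change a participant's NRT without an adverse-event entry, so the pilot's data may, not will, under-report treatment-changing reactions. That conclusion assumes at least one such reaction is both SPC-listed and mild, which the article leaves open, and its size cannot be estimated from the document. The conflict between B.5 and B.8 needs no such assumption; it follows from the wording. Moderate, severe and serious events are unaffected. This is a cheap improvement to the safety record, not a flaw that threatens the trial's conclusions.

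**What to change.** Keep the waiver for mild expected effects and make two edits to Appendix 1.

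1. Add to B.5 that any event, of whatever severity, that leads to a change of dose, a change of product, or temporary or permanent stopping of NRT is always recorded, with the date, the product and the action taken. State whether shorter patch wear counts as a change of dose for this purpose.
2. Limit the causality requirement in B.8 to recorded events, so that it agrees with B.5.

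While B.5 is open, a few words could also say how mild events that are not SPC-listed are handled.

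The cost is a short text change and a small number of extra log entries for the pharmacists. The edits concern recording only and alter no dose, product choice or stopping rule.
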